**Enrollment:**					
Eligibility screen	X				
Informed consent	X				
Allocation		X			
**Interventions:**					
(1) Virtual reality exposure therapy (VRET)			X		
(2) Acceptance and commitment therapy (ACT)			X		
(3) Controls (treatment as usual)			X		
**Assessments:**					
(1) (a) Sociodemographic and clinical characteristics data		X			
(b) Alcohol use characteristics (number of drinks per drinking days, number of hazardous drinks per week or per drinking day, and frequency of binge drinking in previous week)		X	X	X	X

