**Discussion:**

As data on the effects of non-pharmacological interventions, such as VRET and ACT, on the treatment of alcohol craving and preventing relapse in alcohol use disorder are lacking, this RCT fills the research gap by providing these important data to treating clinicians. If proven efficacious, the efficacy of VRET and ACT for the treatment of other substance use disorders should also be investigated in future.

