### 1.1. Alcohol use disorder and the major issue contributed by alcohol craving

One of the commonest negative impacts of alcohol consumption is the occurrence of alcohol use disorder. Alcohol use disorder is a chronic and recurrent mental disorder (5). It will affect the brain's ability to control emotions, decisions, and behaviors, resulting in the decline of work and learning abilities, impaired physical and mental health, and even legal problems (5). Alcohol use disorder poses a serious threat to individual health, family wellbeing, and social stability (6). Therefore, how to effectively treat the disease and prevent relapse is of great significance.

The core symptoms of alcohol use disorder include two aspects: physical dependence based on increased alcohol tolerance and withdrawal reaction and psychological dependence based on alcohol craving (5, 6). Currently, the clinical treatment for alcohol use disorder is focused on reducing physical dependence, and in fact, this is the only effective treatment available for alcohol use disorder. Treatment methods for physical dependence mainly include the prescription of benzodiazepines which is administered to alleviate withdrawal symptoms, low-dose antipsychotic to relieve psychotic symptoms associated with alcohol withdrawal, and adequate vitamin B6 supplementation to prevent Wernicke encephalopathy. However, most patients remain psychologically dependent on alcohol during abstinence, and their hazardous drinking persists due to the satisfaction and euphoria contributed by persistent drinking, resulting from strong alcohol craving (7), even after receiving standardized in-patient treatment. This psychological dependence on alcohol is hard to resist, so it is extremely difficult to maintain long-term abstinence, and hence, alcohol use disorder is prone to relapse (5). Since psychological dependence is the key factor leading to relapse of hazardous alcohol use after abstinence, it is essential to monitor and manage alcohol craving to improve the therapeutic outcome of alcohol use disorder.

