#### 2.9.1. Sociodemographic, clinical, and alcohol use characteristics

The sociodemographic and clinical characteristics recorded from the participants include age, marital status, monthly household income, occupation status, education attainment, history of cigarette smoking, current and lifetime history of medical illness, current and lifetime history of psychiatric illness, and current medication history.

The alcohol use characteristics recorded include duration of alcohol use, average number of drinks during drinking days, frequency of binge drinking in the previous week (binge drinking is defined as five drinks on an occasion in men and four drinks on an occasion for women) (36), and the number of hazardous drinks per day or per week (hazardous drinking is defined as 14 drinks per week or four drinks per drinking day for men and seven drinks per week or three drinks per drinking days for women) (37).

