### 2.10. Data analysis

Data analysis will be carried out using the Statistical Package for Social Sciences version 26 (SPSS-26, Inc., Chicago, IL, USA). Descriptive statistics for sociodemographic, clinical, and alcohol use characteristics, AUDIT, PACS, HAM-D, and HAM-A scores, and ERP will be computed. For nominal and ordinal data, these will be presented in frequency and percentage. For continuous data, it will be presented as mean and standard deviation if the variable is normally distributed. While for non-normally distributed data, it will be presented as median and interquartile range. The normality of the data will be determined by Shapiro–Wilk test.

As for the assessment of the primary outcome, one-way ANOVA with false discovery rate adjustment is used to compare the mean of the outcomes (PACS, average number of drinks during drinking days, frequency of binge drinking in the previous week, and the number of hazardous drinks per day or per week) between the three groups (VRET, ACT, and control groups) at each specific time point (t_0_, t_1_, t_2_, and t_3_). While for the main analysis, mixed ANOVA is used to evaluate the interaction of intervention and time on the outcomes will be computed (outcomes: PACS, average number of drinks during drinking days, frequency of binge drinking in the previous week, and the number of hazardous drinks per day or per week; interaction: intervention × time; whereby time is the within-subject factor, while intervention is the between-subject factor). The main effect of the interaction will be presented as estimated marginal mean and standard error of mean. The primary outcome assessment will follow the intent-to-treat principle. The data analysis for the secondary outcomes (AUDIT, HAM-D, and HAM-A scores and ERP) will be analyzed in the same way as the primary outcomes. Statistical significance is set at *p* < 0.05 and is two-tailed.

As for the management of missing data, if there is only 5% of missing data or less, it will be ignored and data analysis will proceed. However, if the missing data are from 5 to 40% and are missing randomly, multiple imputations with restricted maximum likelihood estimates will be performed using Stata 15, to estimate the missing values. However, if the missing data are more than 40% or are completely randomly missing or non-randomly missing, data analysis of the remaining data will proceed, and the missing data issue will be reported under the limitation of the study (46).

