## 3. Discussion

This study primarily investigates the efficacy of VRET compared with ACT and treatment as usual to depreciate the degree of alcohol craving for people with alcohol use disorder to reduce relapse. In addition, this study also evaluates the efficacy of VRET compared with ACT and treatment as usual to dissipate the severity of alcohol use disorder, and comorbid depressive and anxiety symptoms and normalize the ERP among the alcohol use disorder patients across four timelines (from the baseline to immediately after completion of intervention, 8 weeks after completion, and 20 weeks after completion). The research findings will provide evidence to treating clinicians regarding efficacious psychotherapy or psychosocial intervention for the treatment of alcohol use disorder to reduce the rate of relapse, in which currently available pharmacotherapy has little success. Moreover, if VRET and ACT are proven efficacious to treat alcohol craving, these interventions should also be investigated for their efficacy to treat craving and prevent relapse in other substance use disorders in the near future, whereby the methodology of this RCT could be replicated in future studies.

There are a few limitations to be considered in this study. First, this study only recruits male alcohol use disorder patients, which may limit the generalizability of the study findings as it may not be representative of the entire alcohol use disorder population in China and Malaysia. Second, this study will only recruit subjects with Han ethnicity in China and Malaysian Chinese, which may not be representative of the alcohol use disorder population in China and Malaysia as both countries' populations consist of multi-ethnic background. Finally, the differences in the scheduling of interventions and duration of the session between the VRET and ACT groups may lead to differences in findings due to discrepancies in the settings rather than due to differences in efficacy between the two interventions. However, we attempted to align the scheduling of the sessions in all the three groups as similarly as possible. VRET is scheduled for 25 min/session, five times a week for 20 sessions (total duration = 4 weeks), ACT will be conducted for 1 h/session, two times a week for eight sessions (total duration = 4 weeks), and the control group session is performed at 1 h/session, two times a week for eight sessions (total duration = 4 weeks).

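### The article promises evidence on relapse but neither defines nor measures it, and one of its compared drinking outcomes has no value for abstinent patients

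*Protocol article*

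**What the plan says.** **What is promised.** The Abstract states that data on non-pharmacological treatments "on the treatment of alcohol craving and preventing relapse in alcohol use disorder are lacking, this RCT fills the research gap". Section 3 says the findings will guide clinicians on "efficacious psychotherapy or psychosocial intervention for the treatment of alcohol use disorder to reduce the rate of relapse". Section 1.1 gives the clinical background: "it is extremely difficult to maintain long-term abstinence, and hence, alcohol use disorder is prone to relapse".

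**What is measured.** Patients enter after two weeks of in-patient detoxification (Section 2.6). Table 1 gives the alcohol-use items as "number of drinks per drinking days, number of hazardous drinks per week or per drinking day, and frequency of binge drinking in previous week", at t0 and at weeks 4, 12 and 24. Section 2.9.1 words the three items separately:
- "average number of drinks during drinking days", with no recall window;
- "frequency of binge drinking in the previous week", the only item with a window;
- "the number of hazardous drinks per day or per week", which gives a unit but no window.

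AUDIT (Section 2.9.3.1) is given at the same visits. Three of its ten items concern amount and frequency of drinking, and the article states no recall window for it.

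**How it is analysed.** Section 2.10 puts "average number of drinks during drinking days, frequency of binge drinking in the previous week" and the hazardous-drinks count next to PACS under the primary outcome. All are compared by one-way ANOVA at each time point and by mixed ANOVA, and the primary outcome assessment is to follow intention to treat. The missing-data rule in the same section has three branches: up to 5% missing is ignored; 5 to 40% missing at random is multiply imputed; above 40%, or if missing completely at random or non-randomly, the remaining data are analysed.

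**The concern.** There are two linked problems.

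First, the announced conclusion does not match the measurements. A statement about relapse needs a definition and a record of whether, and preferably when, drinking resumed. The article has neither. The one drinking item with a stated window looks back a week, while the visits close intervals of 4, 8 and 12 weeks. On that item, a patient who binges between visits and has stopped by the week before the next visit looks the same as one who never drank.

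Second, drinks per drinking day has drinking days as its denominator. Abstinence is the state that detoxification and the trial treatments aim for, and the ratio does not exist for patients who achieve it. If they fall out of the comparison, what remains is drinkers against drinkers, groups selected after randomisation by something the treatment may affect. If they are imputed from those who drank, abstinent patients are given drinking amounts. In both cases an arm with more abstinent patients may get no credit for them.

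**Working it through.** The article gives no relapse rate and no episode length, so it has no figure of its own to reproduce here.

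**A. Coverage of the past-week binge item**

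Inputs: visits at weeks 4, 12 and 24 (Table 1, Section 2.9) and a one-week window (Section 2.9.1). The windows are weeks 3–4, 11–12 and 23–24.
- Whole follow-up: 3/24 = 12.5%.
- After treatment ends at week 4: 2/20 = 10%.

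Assume one episode of length D weeks with a start uniform over weeks 0–24. It touches a window ending at week v if it starts between v − 1 − D and v. Any overlap counts as detection, which favours the plan.

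| D (weeks) | Starts that touch a window | Touched | Missed, starts 0–24 | Missed, starts 4–24 |
|---|---|---|---|---|
| 1 | 2–4, 10–12, 22–24 | 6/24 = 25% | 75% | 1 − 4/20 = 80% |
| 2 | 1–4, 9–12, 21–24 | 9/24 = 37.5% | 62.5% | 1 − 6/20 = 70% |
| 3 | 0–4, 8–12, 20–24 | 12/24 = 50% | 50% | 1 − 8/20 = 60% |
| 4 | 0–4, 7–12, 19–24 | 14/24 = 58% | 42% | 1 − 10/20 = 50% |
| 8 | 0–12, 15–24 | 21/24 = 87.5% | 12.5% | 1 − 17/20 = 15% |
| 12 | 0–24 | 24/24 = 100% | 0% | 0% |

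More than half of episodes are missed only if they last under about 3 weeks, or under about 4 weeks for those starting after week 4.

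**B. The ratio for abstinent patients**

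Drinks per drinking day = total drinks ÷ drinking days. With no drinking days in the recall period this is 0/0. The article gives no value for that case. If the blank is handled as missing under Section 2.10:
- at 5 to 40% blank, if judged missing at random, the values are imputed from other patients;
- above 40%, or if judged non-random, the abstinent patients are left out. Non-random is the natural description, because the blank arises from the outcome itself.

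The documents give no abstinence rate. Taking 30 to 60% abstinent at a visit as an assumption, the lower end falls in the imputation branch and the upper end in the drop branch.

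To show the direction of the bias, let arm 1 have 30% abstinent and arm 2 have 60% (the two ends of that assumed range), with drinkers in both arms averaging the same m drinks per drinking day.
- Drinkers only: m against m, difference 0.
- Abstinent patients scored 0: 0.7m against 0.4m, so arm 2 is lower by 1 − 0.4/0.7 = 43%.

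The drinkers-only comparison loses the whole difference. If drinkers in arm 2 were the heavier ones, it would favour arm 1.

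**The case against.** **Relapse is not an objective.** Section 1.6 names craving, disorder severity, depression and anxiety, and ERP. Relapse appears as rationale and in discussion. This stands: no stated objective fails. It is also why withdrawing the relapse wording is an adequate alternative remedy. It does not rescue the claims themselves, which say the trial fills a gap in relapse data.

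**AUDIT also asks about drinking.** It does, at every visit, and no past-week limit is stated for it. So one may not infer that binge frequency is the only post-baseline evidence of drinking. But the article uses AUDIT as a severity score, and it does not date a relapse.

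**Scoring rules belong in the analysis plan.** Section 2.8 says a statistical analysis plan will be prepared, and a zero-score convention could be set there. Nothing in the article says abstinent patients will be excluded, so the bias in part B depends on the blank being treated as missing. What stands is that the article itself fixes an outcome that fails for abstinent patients, and its only stated rule for absent values imputes or drops them.

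**Two stronger readings are tempting and not supported.**
- A reader might infer that all the drinking measures are past-week snapshots. Section 2.9.1 ties the previous week to binge frequency alone. For the other two items the fault is an unspecified window, and the 12.5% does not apply to them.
- A reader might infer that most relapses go uncounted. That needs an assumption about episode length that the documents do not supply, and it is false for sustained relapse. Section 1.1 describes drinking that persists after in-patient treatment, which suggests that longer episodes matter.

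**Conclusion.** The point holds in this form. The article promises evidence on preventing relapse and reducing its rate, but neither defines relapse nor measures whether or when drinking resumed after detoxification. The one stated recall window covers 3 of 24 follow-up weeks, so short binge relapses between visits can be missed. The size depends on an assumed single episode with a uniform start: about 75% missed at 1 week, 42% at 4 weeks, none at 12 weeks or more.

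That drinks per drinking day is undefined without drinking days needs no assumption. The resulting bias depends on the blank being handled under the stated missing-data rule, and its size on abstinence rates that the documents do not give.

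The PACS comparison, which serves the primary objective, is unaffected. The relapse conclusion and the arm comparison on drinks per drinking day are not secure as written.

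**What to change.** 1. In the arm comparison (Section 2.10), replace drinks per drinking day by total drinks over a fixed, stated period, with abstinent patients scored 0. Every assessed patient then has a value.
2. At t1, t2 and t3, add since-last-visit questions to the existing alcohol-use questionnaire: date of first drink, date of first day with five or more drinks (the article's own binge threshold for men), number of drinking days and number of binge days. Keep the past-week binge item.
3. State a definition of relapse and report relapse by week 24 for each arm.
4. If these questions are not added, remove the relapse claims from the Abstract and from Section 3.

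The cost is a few extra questions at visits already scheduled, with no additional visit or test. The downside is recall over up to 12 weeks (from t2 to t3), with some error in dates and counts. Keeping the past-week item preserves one short-recall measure alongside.

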**(2) Primary outcomes:**					
(a) Penn Alcohol Craving Scale (PACS)		X	X	X	X
**(3) Secondary outcomes:**					
(a) Alcohol Use Disorder Identification Test (AUDIT)		**X**	**X**	**X**	**X**
(b) Hamilton Anxiety Rating Scale (HAM-A)		X	X	X	X
(c) Hamilton Depression Rating Scale (HAM-D)		X	X	X	X
(d) event-related potential (ERP) detection in electroencephalogram (EEG)		X	X	X	X

#### 2.9.1. Sociodemographic, clinical, and alcohol use characteristics

The sociodemographic and clinical characteristics recorded from the participants include age, marital status, monthly household income, occupation status, education attainment, history of cigarette smoking, current and lifetime history of medical illness, current and lifetime history of psychiatric illness, and current medication history.

The alcohol use characteristics recorded include duration of alcohol use, average number of drinks during drinking days, frequency of binge drinking in the previous week (binge drinking is defined as five drinks on an occasion in men and four drinks on an occasion for women) (36), and the number of hazardous drinks per day or per week (hazardous drinking is defined as 14 drinks per week or four drinks per drinking day for men and seven drinks per week or three drinks per drinking days for women) (37).

#### 2.9.2. Primary outcome (degree of alcohol craving)

##### 2.9.2.1. Penn Alcohol Craving Scale

This self-administered instrument is used to measure the degree of alcohol craving among alcohol users. It consists of five items in a single factor. Each item is scored on a Likert scale ranging from 0 (none) to 6 (extremely severe). The items are designed to rate the frequency, duration, intensity, average craving degree, and difficulty to cope with craving experienced in the past week. The higher the score, the more severe the degree of alcohol craving (38). The instrument is translated and validated in the Chinese alcohol user population and exhibits an excellent internal consistency with Cronbach's α of 0.97 (39).

#### 2.9.3. Secondary outcomes

##### 2.9.3.1. Alcohol Use Disorder Identification Test

This self-administered tool is used to assess the severity of alcohol use disorder among alcohol users. The tool consists of 10 items and three domains, in which three items are designated to the amount and frequency of the alcohol consumption domain, three items are assigned to alcohol dependence domain, and another four items are allocated to various problems caused by the alcohol domain. It has a cutoff score of ≥8 indicating the presence of alcohol use disorder. A high score in the first three items and a low score in the other items indicate serious harmful drinking, while a high score in items 4, 5, and 6 denotes a significant degree of alcohol dependence, and a high score in the last four items demonstrate hazardous drinking (40). The tool was translated and validated in the Chinese alcohol use disorder population, and its internal consistency was acceptable with Cronbach's α of 0.782 (41).

##### 2.9.3.2. Hamilton Depression Rating Scale

The HAM-D is an observer-administered instrument to assess the severity of depressive symptoms. The HAM-D consists of 21 items but is scored on the first 17 items. The higher the score, the greater the severity of depressive symptoms. The interpretation of the total score is such that the score of 0–7 indicates normal, 8–16 denotes mild depression, 17–23 indicates moderate depression, and 24 and above denotes severe depression (42). The instrument is translated and validated in the Chinese population with an acceptable internal consistency with Cronbach's α of 0.714 (43).

##### 2.9.3.3. Hamilton Anxiety Rating Scale

The HAM-A is an observer-administered instrument to assess the severity of anxiety symptoms. It consists of 14 items which assess 14 anxiety symptoms. Each item is scored on a Likert scale ranging from 0 (not present) to 4 (severe). A total score of <17 indicates mild severity, 18–24 denotes mild to moderate severity, 25–30 indicates moderate to severe, and >30 indicates severe (44). The instrument is translated and validated in the Chinese population with an excellent internal consistency with Cronbach's α of 0.93 (45).

##### 2.9.3.4. Event-response potential

###### 2.9.3.4.1. Experimental paradigm.

Visual stimuli will be presented by E-Prime 2.0 software. There are three types of visual stimuli, such as (a) images related to alcohol cues (for example, common places where alcohol is consumed, habitual alcohol products, and people drinking alcohol), (b) neutral images which are not related to alcohol cues, and (c) task-related images which require key operation. The EEG monitoring and recording will be carried out, while the participants watch the stimulation paradigm.

###### 2.9.3.4.2. Acquisition of EEG signal.

EEG signal monitoring and recording are performed using the Brain Amp MR-32 instrument and Brian Vision Recorder software. A total of 64 scalp positions will be recorded by using the 10-10 standard lead system. The sampling rate will be adjusted to 1,000 Hz, and the impedance between the electrodes and the skin of the scalp will be < 5 kΩ.

###### 2.9.3.4.3. ERP analysis.

The data analysis for ERP will be carried out using Brian Vision Analyzer 2.1 software. The processes involved are re-reference, filtering, removal of ocular artifacts, artifact removal, segmentation, baseline correction, and peak detection.

##### 2.9.3.5. Other measures

An electronic diary will be created which allows the participants to record their progress in doing home assignments between each ACT session, to ensure that the practice of ACT strategies learned in each session is consolidated. In addition, any dropout from the study and its reasoning (lack of interest to continue, being ill, transportation, and logistic issues) will also be recorded.

